##### Screening assessment

As information from e-SUS database is not frequently updated, we will ask the UBS managers and CHWs to pre-screen a list of around 150 names per FHT in order to identify individuals who we will not be able to find (dead or moved to another area) and those who present clinical exclusion criteria. We will also ask the CHWs to update the individuals’ contact information.

The RA from the sub-contracted company will follow the random order of names on the list to contact individuals for screening. The contact will be by phone or home visit, and there will be at least one contact attempt through a home visit before excluding any individual from the study.

##### Baseline assessment

If the individual scores 10 or above on the PHQ-9 (screening interview) and does not present any exclusion criteria, he/she will be invited to the baseline assessment. All baseline interviews will be conducted by a home visit. If the screening interview is conducted by phone, at the end of the interview, the RA will schedule a home visit to conduct the baseline assessment. If the screening is conducted by a home visit, the researcher will proceed to the baseline assessment on the same day of the screening whenever possible, after obtaining the participant’s written consent to enter the trial. In situations where the individual prefers to continue with the baseline interview on another day, the RA will schedule a new home visit.

Soon after recruitment is completed in each UBS, the study coordinator will send a list to UBS managers (both study arms) with the names of all individuals from their clinics who agreed to participate in the study. The UBS manager will be advised by the study coordinator to inform the relevant FHT members about the individuals under their care who are participating in the study. From this point, the FHTs will manage these individuals with depression according to usual practice. In the intervention arm, besides informing UBS managers about the participants included in the study, the clinical supervisor from each UBS will also receive a list with the names of all study participants before assigning them to the CHW who will conduct the psychosocial intervention.

## Assignment of interventions: allocation

### Sequence generation {16a}

#### Clusters

UBSs will be identified, approached to participate and then randomised at the beginning of the study. For stratification, we will use the educational level (percentage of individuals with no education or who had completed a literacy programme for adults) collected through the e-SUS database of the individuals 60 years or older registered with each UBS. Stratification will be into two sets of UBSs (according to whether they are above or below the median on this educational variable). Four UBSs will be randomly selected as reserves (two from each stratum), in case a UBS decides subsequently to not take part in the study. Of those 20 remaining UBSs, 10 will be randomly allocated to each arm of the trial (five from each stratum). Also, four FHTs within each UBS will be randomly selected to be part of the study.

### Concealment mechanism {16b}

Not applicable at the level of the individual participant given the nature of this cluster randomised trial, though the UBSs (clusters) will all be recruited before allocation to the trial arm is conducted.

### Implementation {16c}

The Bristol Randomised Trials Collaboration (through a merger, now part of the Bristol Trials Centre), which is a UK Clinical Research Collaboration fully registered Clinical Trials Unit, will conduct the randomisation of the UBSs and FHTs, by an individual ([name]) not involved in the trial recruitment process at any stage. Allocation/selection will therefore be conducted remotely by an individual not involved in the recruitment and will be conducted only after all UBSs have formally confirmed their participation in the trial.

## Assignment of interventions: blinding

### Who will be blinded {17a}

Complete blinding of participants or CHWs to trial allocation is impossible given the nature of this intervention. To decrease the risk of observer bias at follow-up, the two follow-up assessments will be made by RAs who are not involved in the initial recruitment or in delivering the intervention. We will rotate these RAs so that unless it is unavoidable the same researcher does not conduct any interview with the same participant more than once. We will also ensure that the primary data analysis is completed blind to trial allocation.

### Procedure for unblinding if needed {17b}

Unblinding will occur only after the analysis of primary endpoints has been completed, and likewise after as many of the secondary outcomes are considered as is feasible before unblinding becomes impossible to avoid.

## Data collection and management

### Plans for assessment and collection of outcomes {18a}

#### Collection of trial data

Individual data will be gathered and stored electronically in an information technology system developed for the management of this study. Participants consenting to the trial will be informed of this and receive an ‘ID number’ when entering the study. All data will be linked using ID codes to identify the person. A list of IDs will be kept in a secure place with access only to the joint principal investigators. Data will be captured via digital recorders, tablets and on paper when necessary. Screening, baseline and follow-up data will be collected by a sub-contracted company using a software provided by the research team, and all data will be stored in the study server. The sub-contract with the company will ensure that access and protection of the data is consistent with Medical Research Council guidelines and National Health Council (Conselho Nacional de Saúde—Brazil) (Resolution 196/96-2012) regulations. A quality control assessment of a sample of the audio recordings will be conducted by an independent researcher trained by the research team. The main aim of this quality control is to ensure that all procedures have been correctly followed by the RAs and all information has been given to the participants. The research team will also supervise the work of this company using a web interface developed to follow live updates of the assessment’s status.

All data will be kept in a secured server at the University of São Paulo. Digital files will be stored anonymised in password-protected directories on secure computers.

We will use data recorded routinely with the app (number and duration of psychosocial treatment sessions, other actions performed at the sessions) to assess the fidelity with which the intervention was delivered. A detailed record of all clinical data will be kept. We will record the training time for all staff involved in the study.

#### Instruments

The three main instruments used in this study are the PHQ-9 (at the screening and follow-up assessments), the EQ-5D-5L and the ICECAP-O.

The PHQ-9 [30, 44] is a well-validated brief depression measure extensively used in clinical research, including Brazil [45], among other reasons because it is sensitive to changes over time [44, 46]. Acute suicide risk will be assessed with a standardised questionnaire whenever the ninth question of the PHQ-9 is scored 1 or more.

The EQ-5D [34, 47] is a generic preference-based outcome measure that provides a common metric for policy-makers to compare the cost-effectiveness of treatment in diverse clinical settings. The EQ-5D is sensitive to changes in mental health outcomes in the literature [48, 49], and the new five-level version was correlated with changes in the PHQ-9 scores in the pilot study [22].

The ICECAP-O [35] measure will be used to assess broader wellbeing/capability (for example, independence, security) of participants. We have registered the intention to use both EQ-5D and ICECAP-O instruments with the developers of these instruments.

We will also collect information on participants’ sociodemographic profile, health condition, anxiety symptoms (GAD-7) [37], social network (Lubben Social Network Scale-6—LSNS-6 [50, 51]), stressful life events [38], smoking habits, alcohol use (Alcohol Use Disorders Identification Test-Consumption—AUDIT-C) [52], disability, behaviour activation (BADS-SF) [36], loneliness (3-item University of California, Los Angeles (UCLA) loneliness scale) [53], work loss productivity, use of private care, need of care, use of medication for chronic conditions, consultations with healthcare professionals and admission to hospital. The economic assessment will also include resources used during the CHW training and supervisory sessions and data collected from medical records and the public health system databases (consultations and procedures).

### Plans to promote participant retention and complete follow-up {18b}

We will inform participants from both arms about the approximate date of the two follow-up interviews. Follow-up assessments will ideally be conducted face-to-face, but it can also be conducted by phone when necessary. We decided to include a time ‘window’ to reflect the logistical realities of the context and to maximise response to follow-up. If any participant from either arm is not contactable for the follow-up interview, we will contact the neighbours and the UBS managers to confirm current contact details.

### Data management {19}

The electronic data will be stored in our server, which has several mechanisms to ensure that data remain confidential and inaccessible to others than those with access rights. The principal investigators will be responsible for data security. All computers used in this project will be password protected, and access to data files archived will also be password protected. There will be a database backup updated daily and stored in a different secure server at the University of São Paulo and mirrored on a server in Limerick, Ireland, where the information technology platform has been developed. The study will be compliant with the UK’s and Brazil’s regulations on research data management. A summary of the data management will be included in the Informed Consent Form given to participants.

We will create a data dictionary, with detailed information on labelling and codes, and describe data, annotations and variables in such a way as to make possible to use by authorised third parties.

Once data are entered to the main database, it will be locked and no further changes are allowed to the original version, albeit with (auditable) changes made in subsequent versions following (usual) data checking processes.

### Confidentiality {27}

All data storage in Brazil will be compliant with the National Commission of Ethics in Research (Comissão Nacional de Ética em Pesquisa), Resolution 466/2012 security policies. All data kept in computers will be anonymised. Paper records will be kept to a minimum and stored in secure storage facilities. Any personally identifiable paper record will be stored separately from anonymised paper records. All electronic records will be stored on password-protected servers. All data will be encrypted to ensure its security. We will put in place any required limitations on data sharing that serve to safeguard the privacy of research participants.

The University of São Paulo has a modern network infrastructure and clear procedures to ensure confidentiality of the data. Parallel storage systems are located at a different location and backed up regularly. Access to data files is controlled by login and password authentication. The data generated and collected through this project will be maintained with the level of security available.

### Plans for collection, laboratory evaluation and storage of biological specimens for genetic or molecular analysis in this trial/future use {33}

There will be no biological specimen collection for this clinical trial.

## Statistical methods

### Statistical methods for primary and secondary outcomes {20a}

#### Primary analysis

The analysis and presentation of data will be in accordance with the Consolidated Standards of Reporting Trials guidelines [54], with the primary comparative analysis being conducted on an intention-to-treat basis (including only those individuals with known primary outcome and emphasis placed on confidence intervals for between-arm comparisons). Descriptive statistics of demographic and clinical measures will be used to ascertain any marked imbalance between the trial arms at baseline. The primary comparative analysis will employ random-effects multivariable logistic regression on the primary outcome to obtain an odds ratio of recovery between the arms at 8 months after adjusting for baseline PHQ-9 scores, stratification and cluster design.

#### Secondary analyses

Other secondary analyses will include (a) comparison of the primary outcome measure at 12 months and using the PHQ-9 score as a continuous variable at both follow-up times (including the use of repeated measures regression models), (b) repeating the analysis for the primary outcome adjusting for any observed imbalance between arms of potential predictor variables at the level of the individual and/or the UBS (introduction of the latter would involve the use of suitable multi-level models) and (c) similar analyses for secondary outcomes for participants at 8 and 12 months. In addition to the adjustment for clustering by (allocated) UBS in the primary analyses, multi-level models will be employed to investigate the extent to which the primary analyses were affected by various clustering effects—UBSs, FHTs and CHWs.

#### Economic analysis

The primary economic analysis will take a Brazilian public health system perspective. Quality-adjusted life years (QALYs) over the 12-month follow-up period will be calculated based on EQ-5D-5L responses using the most appropriate EQ-5D-5L value set available at the time of the analysis. In the primary analysis, the incremental costs and QALYs of the psychosocial intervention will be combined to estimate the incremental net monetary benefit of the intervention at a range of ‘willingness-to-pay’ thresholds. We will also estimate cost-effectiveness acceptability curves to illustrate the probability that the intervention is cost-effective at a range of thresholds. In a secondary analysis, we will estimate the incremental cost-effectiveness ratio of the psychosocial intervention compared to enhanced usual care using the primary clinical outcome measure (i.e. cost per patient recovered at 8 months).

### Interim analyses {21b}

In terms of the statistical and economic analyses of the trial, we do not envisage conducting any between-arm comparisons as interim analyses. The database will be locked by the transaction manager after quality controls. The only reason to check this database before completing the trial is when there is a major concern about the health and/or wellbeing of a participant. However, this would involve only the participant concerned, and this information may need to be shared with others involved in the safety of participants.

### Methods for additional analyses (e.g. subgroup analyses) {20b}

Exploratory subgroup analyses will be undertaken to investigate potential differential effects of the intervention according to pre-specified characteristics of the participants. While the list of potential effect modifiers will be finalised prior to publishing the Statistical Analysis Plan for the trial, the current plan is to consider at least some of the following: gender, age (as a continuous or grouped variable), educational level, presence of co-morbid physical illnesses and severity of depression (the continuous PHQ-9) at baseline. Such analyses will be interpreted cautiously, partly because we do not have an overwhelming single prior hypothesis for these analyses and partly because statistical power will be limited for the required interaction effects within the relevant regression models.

### Methods in analysis to handle protocol non-adherence and any statistical methods to handle missing data {20c}

Sensitivity analysis using multiple imputation models for missing values will be conducted to investigate the potential effects of missing data and attrition. Further secondary analyses will compare individuals according to the intervention they received, accounting for any selection effects after random allocation using complier-average causal effect methods employing instrumental variables regression models. These analyses will first use a binary definition of an ‘adequate dose’ of the intervention, as follows: in the low-intensity group, a minimum of 6 sessions; in the high-intensity group, a minimum of 7 sessions. We will also conduct these analyses according to the number of sessions attended.

### Plans to give access to the full protocol, participant level-data and statistical code {31c}

Summary information of the datasets will be published in relevant research data repositories and directories. Our data will be locked until our main hypothesis-based analyses are completed and published or for 3 years after completion of data collection (whichever is earlier), after which the data will be accessible for external use. The research team has interest in mutually sharing and pooling metadata with other research groups. Data will not be shared with any other source or used for any other purpose other than those approved by the Ethics Committees.

We plan to maximise the availability of research data with as few restrictions as possible, ensure that data should be released in a format that conforms to agreed standards, especially where this allows interoperability with other relevant datasets, require that all users of data acknowledge the sources of their data and conform with the terms and conditions under which they accessed the original data, and put in place any required limitations on data sharing that serve to safeguard the privacy of research participants.

We will implement a data management and sharing plan. This plan will specify the roles, responsibilities and relationships of key persons involved in the research: the applicant, sponsors and collaborators, research team members, research participants and research institutions.

The joint principal investigators, in consultation with a Data Access Committee, will be responsible to grant access to the data, which will be in compliance with sponsors’ regulations. There will be a form to fill to request access to the data. The joint principal investigators will review and approve any such requests. Thus, study data will be made available to researchers after written requests spelling out the specific aims and plan of analysis. If there are conflicts of interest or requests to use data for purposes other than those approved by the Ethics Committee, we will seek advice from them to resolve any such disputes if they ever occur. Data sharing will be in compliance with the principles outlined in Good Practice Principles for Sharing Individual Participant Data from Publicly Funded Clinical Trials. External users will be bound by appropriate data sharing agreements with the Ethical Committee and in line with sponsors and funders’ policies.

## Oversight and monitoring

### Composition of the coordinating centre and Trial Steering Committee {5d}

#### Coordinating centre

University of São Paulo, São Paulo, Brazil.

#### Trial Steering Committee (TSC)

The TSC will meet once a year and is composed of:

### Adverse event reporting and harms {22}

In this study, serious adverse event (SAE) data will be collected—that is, any untoward medical occurrence that is believed by the investigators to be causally related to study intervention. SAEs can result in any of the following: death, attempted suicide, life-threatening situations (that is, immediate risk of death) or significant physical or emotional disability/incapacity. SAEs of individuals who discontinued participation will not be reported. CHWs and sub-contracted RAs will be trained to obtain SAE information from visits. The intervention coordinator will be responsible for the completion of SAE forms and contacting the principal investigator, when necessary. Where appropriate, reports should be forwarded promptly to the Ethics Committee of the USP Medical School, with a copy to the DMC chair. A SOP for SAE recording, management and reporting was also developed to guide the team.

We do not think that this trial poses any considerable risks to trial participants. The intervention to be evaluated adds to existing usual care, and the trial does not prevent family doctors or other FHT professionals initiating or changing treatment for depression or any other health problem. None of the components to be tested is considered harmful.

The risk of suicide among depressed participants will be assessed regularly, and participants at high risk at any stage will receive immediate support from the sub-contracted RA or CHW, something that does not occur at present. CHWs and sub-contracted RAs will be trained in assessing risk with a standardised protocol, and CHWs will also receive ongoing supervision of their cases. A safety plan has been developed to deal with these emergencies and tested during our pilot study with two participants at risk of suicide while receiving the pilot psychosocial intervention. The safety plan was applied successfully by the CHWs in the pilot study. As part of this safety plan, these participants were seen by the family doctor for further assessment and subsequently managed by the FHT.

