## Interventions

### Explanation for the choice of comparators {6b}

The control arm participants will receive an enhanced usual care, while the intervention arm participants will receive both an enhanced usual care and a collaborative care psychosocial intervention. The main component of the intervention is a psychosocial programme delivered at home by trained CHWs who have additional support through weekly supervision and an application installed on tablet computers.

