### Intervention description {11a}

#### Enhanced usual care

This comprises improved recognition of depression by the research team (screening with the PHQ-9 to identify depression) followed by usual care. The research team will send a list with the names of the individuals included in the study to UBS managers (in the control and intervention arms). The research team will not interfere with usual care—for instance, prescription of medications, CHW usual monthly home visits or access to family doctors or mental health specialists.

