#### Individuals who will perform the intervention

Within each of the sampled FHTs, selection of the CHWs to be involved in the study (three per FHT and hence 12 per UBS) will be decided by the UBS manager and the FHT members, consistent with what would happen in practice. A total of 120 CHWs will be selected to conduct the intervention. Additional CHWs will be trained to replace the selected CHWs for a short time in case of annual leave, health issues or any other situation where replacement is required. There is no need to select CHWs in the control arm.

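### Relatedness is built into the SAE definition, so reported SAEs cannot be compared by arm; separately, SAEs of people who discontinue are dropped

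*Protocol article*

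**What the plan says.** All under Adverse event reporting and harms {22} unless another section is named.

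- SAE data will be collected, and an SAE is "any untoward medical occurrence that is believed by the investigators to be causally related to study intervention".
- The serious outcomes are given as possible consequences of such an event: "SAEs can result in any of the following: death, attempted suicide, life-threatening situations (that is, immediate risk of death"), followed by significant disability or incapacity. They are not a free-standing definition.
- "SAEs of individuals who discontinued participation will not be reported".
- Sources of information: "CHWs and sub-contracted RAs will be trained to obtain SAE information from visits". The intervention coordinator completes the forms. An SOP for SAEs is mentioned but is not part of the article.
- On what is being tested: "The intervention to be evaluated adds to existing usual care". Explanation for the choice of comparators {6b} agrees: "The control arm participants will receive an enhanced usual care, while the intervention arm participants will receive both an enhanced usual care" and the psychosocial programme.
- On enhanced usual care (Intervention description {11a}): "This comprises improved recognition of depression by the research team (screening with the PHQ-9 to identify depression) followed by usual care".
- On the community health workers (Recruitment {15}): "There is no need to select CHWs in the control arm".

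**The concern.** Seriousness and causality are two different judgements. A randomised comparison of harms needs the first recorded in the same way in both arms. The second can be added later and should not decide which events are counted. Here the causal judgement is the entry condition, and it refers to something that only one arm receives.

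The population is depressed people aged 60 or over, so deaths and suicide attempts are the events a reader will want to see by arm. Under the written rule the SAE table could show neither an excess of these events nor a reduction in them. A report of few or no SAEs would say little about how many people died or attempted suicide.

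The discontinuation rule is a second, independent loss. If leaving the trial is connected with deterioration, the missing events are not a random subset.

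**Working it through.** The article states no SAE rate, count or safety power, so there is no safety figure to reproduce. The check is a reading of the rules, followed by an illustration of scale.

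**1. Who can have a reportable SAE?** The event must be believed to be caused by the study intervention. The harms section describes the intervention under evaluation as an addition to usual care, and controls receive enhanced usual care only. An event cannot be caused by a programme the person did not receive. On this reading the control count is zero whatever happens to control participants. If PHQ-9 screening were also counted as study intervention, the count would be near zero instead.

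**2. Scale.** Inputs:
- Participants per arm: 72 per cluster × 10 clusters = 720 (Sample size {14}).
- p = true 12-month risk of the listed outcomes. Assumed: 2%, 5% or 10%.
- f = share of events judged related. Assumed: 0 to 25%.

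True events per arm = 720 × p. Reported events = 720 × p × f in the intervention arm and 0 in controls.

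| p, equal in both arms | True events per arm | Reported, intervention (f = 0 to 25%) | Reported, control |
|---|---|---|---|
| 2% | 14.4 | 0 to 3.6 | 0 |
| 5% | 36 | 0 to 9 | 0 |
| 10% | 72 | 0 to 18 | 0 |

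**3. Can the reported counts separate harm from no harm?** Take a control risk of 5% (36 events).
- No effect: 36 v 36 true, reported as 0 to 9 v 0.
- Doubled risk with the intervention (10%): 72 v 36 true, reported as 0 to 18 v 0.
- Reduced risk with the intervention (2%): 14.4 v 36 true, reported as 0 to 3.6 v 0.

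The reported ranges overlap and the control figure never moves. The result depends on f, the causal judgement, as much as on the effect.

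**4. Discontinuation.** This rule applies in both arms and plays no part in the control zero. Consent provision {26b} asks participants whether their data may be used if they withdraw, but the harms section drops the SAEs without regard to that answer. The planned attrition of 15% would be 0.15 × 720 = 108 people per arm. Attrition and discontinuation are not the same thing, so this shows only how many people could be affected.

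**5. Ascertainment.** Intervention participants are planned to have 3 + 5 = 8 or 3 + 8 = 11 home sessions with trained community health workers. Control participants keep their usual monthly visits, but no study training of those workers is described. The research-assistant interviews at 8 and 12 months are the only route clearly common to both arms. This asymmetry matters once the definition is corrected; it adds nothing to a count that is already structurally zero.

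**The case against.** The strongest defence is that the trial collects other information on harm. The PHQ-9 is repeated at follow-up, with a standardised suicide-risk questionnaire whenever item 9 scores 1 or more. Hospital admission is recorded. Both arms are interviewed at 8 and 12 months by assistants not involved in recruitment or delivery, and people who cannot be reached are traced through neighbours and unit managers, so many deaths should come to light. This stands in part: a limited comparison of deterioration, suicide risk and admissions is possible. But the article does not name these as safety outcomes, and they do not count deaths or suicide attempts.

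A second defence is that enhanced usual care is listed under the intervention description and that the assistants, who see both arms, are trained to obtain SAE information. The text is not wholly unambiguous, but the harms section's own description of the intervention points the other way. The SOP is not shown, and it cannot be presumed to reverse a definition that the protocol states.

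Several stronger readings are tempting, and the documents do not support them:

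- *Control-arm harm is zero, or harms cannot be compared at all.* Only the reportable SAE count is zero or near zero.
- *The discontinuation rule contributes to that zero.* It is a separate problem affecting both arms.
- *Causality is judged by unmasked investigators.* The blinding section covers participants, community health workers, follow-up assessors and the primary analysis. It does not state the masking of whoever judges relatedness.
- *A suicide attempt or deterioration is a likely reason to leave.* The listed reasons for stopping the intervention are moving away and participant request. A link with harm is possible but not documented.
- *The DMC sees no harms by arm.* Some reports are copied to its chair, but its full safety remit cannot be judged from the text reviewed.

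**Conclusion.** The point holds for reported SAEs. Because relatedness is the entry condition, serious events judged unrelated are not counted in either arm, and controls can have essentially none that qualify. The reported counts therefore cannot support a between-arm comparison. Separately, events in people who discontinue are lost in both arms, including people who have agreed to continued use of their data.

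The size cannot be fixed from the article. Under the assumed equal risks of 2% to 10%, 14.4 to 72 true events per arm would be reported as 0 in controls and as 0 to 18 at most in the intervention arm. The conclusion does not depend on those assumptions, because the control figure is the same at any risk. It does rest on reading study intervention as the psychosocial programme; the wider reading changes zero to near zero.

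The primary outcome, its analysis and the power calculation are unaffected. What is compromised is the trial's ability to report serious harm or protection by arm.

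**What to change.** - Define an SAE by the seriousness outcomes already listed, regardless of cause, in both arms, from consent to the 12-month follow-up.
- Record relatedness as a separate judgement on each event.
- Delete the sentence excluding people who discontinued, and continue collection unless consent for data use is withdrawn.
- Base the between-arm comparison on identical questions put by the research assistants at the 8- and 12-month interviews, plus deaths found when tracing participants.
- Show events found only at community health worker sessions separately, because that route is far more intensive in the intervention arm.
- Report counts by arm.

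The cost is more SAE forms, a few interview items, changes to protocol and SOP wording, and an approved amendment. Recruitment began in May 2019, so events in people already enrolled would have to be captured retrospectively at their follow-up interviews. The report should state which participants were covered prospectively. The pause in recruitment described under Trial status, where amendments are already foreseen, makes the change practicable.
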